## ▪ STUDY SUMMARY

|                                                  |                                                                                                                                                           |
|--------------------------------------------------|-----------------------------------------------------------------------------------------------------------------------------------------------------------|
| Title                                            | Head Shaking and Mastoid Oscillation Maneuvers in Posterior Canal-Benign Paroxysmal Positional Vertigo-Cupulolithiasis (PC-BPPV-cu)                       |
| Supervision institution & Principal investigator | Department of Neurology, Pusan National University Hospital
[name] (Professor)                                                                |
| Funding agency                                   | Memorial Foundation for [name] by named Hyangseal, Korean Neurological Association (KNA-21-HS-08)                                                 |
| Study Purpose                                    | The purpose of this study is to determine immediate and short-term therapeutic efficacies of head-shaking and mastoid oscillation maneuvers in PC-BPPV-cu |
| Study design                                     | Multi-center, double blind, randomized controlled trial                                                                                                   |
| Study period                                     | IRB approval date ~ 4 years                                                                                                                               |
| Target population                                | Subjects with PC-BPPV-cu confirmed at the participating clinics during the study period.                                                                  |
| Number of subjects                               | 159 subjects (53 for each arm)                                                                                                                            |
| Vulnerable person                                | Not applicable                                                                                                                                            |
| Investigational product                          | Not applicable                                                                                                                                            |
| Usage and dosage                                 | Not applicable                                                                                                                                            |

|                              |                                                                                                                                                                                                                                                                                                                                                                                                                                                                                                                                                                                                                                                                                                                                                                                                                                                                                                                  |
|------------------------------|------------------------------------------------------------------------------------------------------------------------------------------------------------------------------------------------------------------------------------------------------------------------------------------------------------------------------------------------------------------------------------------------------------------------------------------------------------------------------------------------------------------------------------------------------------------------------------------------------------------------------------------------------------------------------------------------------------------------------------------------------------------------------------------------------------------------------------------------------------------------------------------------------------------|
| Study methods                | 
 
1) Subjects with PC-BPPV-cu confirmed at each clinic will be randomly assigned (1:1:1) to the head shaking, mastoid oscillation, or control group using an interactive web response system.
 
2) A treatment maneuver will be performed once by a physician according to assigned treatments or sham group.
 
3) The treatment response will be determined by participating neurologists in each clinic without knowing the maneuver applied to each patient at 30 minutes after initial maneuver.
 
4) When the subjects will show positioning nystagmus, they will receive the previously applied maneuver again.
 
5) The subjects will undergo re-examination 30 minutes later and will be scheduled for follow-up the next day without additional treatment if they will still present with positional vertigo and nystagmus.
 
 |
| Target disease               | Posterior Canal-Benign Paroxysmal Positional Vertigo-Cupulolithiasis                                                                                                                                                                                                                                                                                                                                                                                                                                                                                                                                                                                                                                                                                                                                                                                                                                             |
| Inclusion/exclusion criteria | 
Patients who meet the following inclusion and exclusion criteria.
 
Inclusion criteria
 
 
1) A history of recurrent attacks of positional vertigo
 
2) Positional nystagmus beating torsionally with the upper pole of the eye to the lower ear and vertically upward (to the forehead) and lasting > 1 min which was evoked by Dix-Hallpike or half Dix-Hallpike maneuver
 
3) Absence of identifiable CNS disorders that could explain the positional vertigo and nystagmus.
 
 
Exclusion criteria
 
 
1) Younger than 20 years
 
2) Subjects with multicanal BPPV, cervical spinal problems, or cognitive dysfunction
 
3) Subjects for whom, according to the investigators' opinions,
 
                                                             |

|                      |                                                                                                                                                                                                                                                                                                                                                                   |
|----------------------|-------------------------------------------------------------------------------------------------------------------------------------------------------------------------------------------------------------------------------------------------------------------------------------------------------------------------------------------------------------------|
|                      | 
participating in this clinical trial would pose a serious danger to their well-being or would result in unreliable outcomes at the end of the study.
 
4) Subjects with severe, acute, chronic, progressive, or degenerative diseases that may affect this clinical trial.
 
5) Subjects who do not agree to participate in this clinical trials
 |
| Efficacy evaluation  | The resolution of both positional vertigo and nystagmus                                                                                                                                                                                                                                                                                                           |
| Safety evaluation    | Not applicable                                                                                                                                                                                                                                                                                                                                                    |
| Visit schedule       | Subjects will be scheduled to return to the clinic the next day if the vertigo and nystagmus will not resolve after two randomized maneuvers on the day of the visit.                                                                                                                                                                                             |
| Statistical analysis | Any difference in the treatment response would be determined using ANOVA and Chi-square test between the treatments and control groups.                                                                                                                                                                                                                           |
| Expected effects     | The head shaking and mastoid oscillation maneuvers would be recommended as initial treatment options for PC-BPPV-cu.                                                                                                                                                                                                                                              |

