## ▪ STUDY PROCEDURES

| Study procedure                     | V1              |               | V2 (V1+1day)                                                  |               |
|-------------------------------------|-----------------|---------------|---------------------------------------------------------------|---------------|
|                                     | Treatment group | Control group | Treatment group                                               | Control group |
|                                     |                 |               | When the subjects still have positional vertigo and nystagmus |               |
| Informed consent                    | X               | X             |                                                               |               |
| Demographics assessment             | X               | X             |                                                               |               |
| Inclusion/exclusion criteria        | X               | X             |                                                               |               |
| Medical history                     | X               | X             |                                                               |               |
| Assessment of dizziness history     | X               | X             |                                                               |               |
| Neuro-otological examinations       | X               | X             |                                                               |               |
| Positional test                     | X               | X             | X                                                             | X             |
| Canalith repositioning maneuver     | X               | X             |                                                               |               |
| Determination of treatment response | X               | X             | X                                                             | X             |
| End of study                        |                 |               | X                                                             | X             |

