BPPV was traditionally considered as a benign condition that often resolved spontaneously over time without specific treatment. On average, PC-BPPV resolved about 39 days later. However, for the effective management of BPPV and to alleviate dizziness, accurate diagnosis and canalith repositioning maneuvers (CPM) are recommended.

Previous randomized controlled trials have proven that head-shaking and mastoid oscillation maneuvers effectively treat cupulolithiasis of the horizontal canal benign paroxysmal positional vertigo (HC-BPPV-cu). However, no data exist regarding the therapeutic efficacy of these maneuvers in PC-BPPV-cu.

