## **5) TRIAL ENDPOINTS**

- A. Primary endpoint: The overall short-term resolution rate of positional vertigo and nystagmus in the following day.
- B. Secondary endpoint: The immediate efficacy of two trials of each maneuver within 30 minutes.

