## 8. STATISTICS

### 1) DESCRIPTION OF STATICS METHODS

The demographic distribution of study participants by treatment maneuvers were compared using the Chi-squared test and one-way analyses of variance (ANOVA). If the results of the Chi-squared test were significant, additional post-hoc tests were performed using Bonferroni adjusted alpha level of 0.0167 per test (0.05/3). Statistical analyses were performed using SPSS (version 27.0; SPSS, Chicago, IL, USA).

The primary outcome was analyzed using both intention to-treat and per-protocol methods. Patients who did not complete the assessment in the following day were excluded from the per-protocol analysis.

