### **4) PARTICIPANT CONFIDENTIALITY**

- A. The trial staff will ensure that the participants' anonymity is maintained, and even when the study results are published, the participants' identities will be kept confidential.
- B. The personal information of the participants collected for this study will be the date of birth and sex.
- C. All documents related to the study, such as the CRF, should be recorded and classified by the subject identification code and participants' initials rather than the participants' names.
- D. Electronic data will be saved in a password-protected file, and documents that need to be kept as a paper will be stored in a locked documents box.

- E. All documents related to the study will be kept for 3 years from the time the study is completed, and the data for which the storage records have been completed will be destroyed in accordance with Article 16 of the Enforcement Decree of the Personal Information Protection Act.

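### Treatment response is to be compared without baseline adjustment although age, sex and dizziness history are collected at V1; prespecified adjustment would be a cheap gain in efficiency, not the repair of an error

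*Protocol*

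**What the plan says.** - **Outcome analysis** (Study Summary, Statistical analysis): "Any difference in the treatment response would be determined using ANOVA and Chi-square test between the treatments and control groups". No covariate is named here or in Section 8.
- **Primary endpoint** (Section 7, Trial endpoints): "The overall short-term resolution rate of positional vertigo and nystagmus in the following day". Resolution needs both vertigo and nystagmus to be absent, so each participant's outcome is yes or no.
- **Baseline data**: the Study Procedures table marks "Demographics assessment" and "Assessment of dizziness history" at V1 for treatment and control groups. Section 9, Participant confidentiality, adds: "The personal information of the participants collected for this study will be the date of birth and sex". Age and sex are therefore available for everyone.
- **Stated use of the demographics** (Section 8, first subsection): "The demographic distribution of study participants by treatment maneuvers were compared using the Chi-squared test and one-way analyses of variance (ANOVA"). The next sentence sets post-hoc tests at a "Bonferroni adjusted alpha level of 0.0167 per test (0.05/3").
- **Natural course** (Section 5, Study background): "On average, PC-BPPV resolved about 39 days later".

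**The concern.** The protocol names a method for judging treatment response, and that method uses nothing known about the participant before the maneuver. If some of that information predicts resolution, a prespecified adjusted analysis gives a more precise treatment comparison from the same 159 people. The protocol gives some reason to think prognosis varies: it describes spontaneous resolution and plans for 38% resolution under sham.

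The one stated use of the demographics does not serve this purpose. Under sound randomization, a significance test of baseline balance can only detect chance, and it leaves the treatment estimate unchanged. The protocol also does not say what follows if age, for example, differs at p < 0.05. That leaves room for adjustment chosen after the results are known. Naming the covariates in advance closes that gap, whatever their strength.

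**Working it through.** **Inputs from the protocol.** Resolution 70% with a maneuver and 38% with sham; alpha 0.0167, two-sided because the printed formula uses Z at alpha/2; power 80%; ratio 1:1:1; dropout 5%; 53 per arm, 159 in total. The planning rates are for immediate resolution. They are used here because the protocol gives no others.

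**Step 1: reproduce the plan's figure.** The mean rate is (0.70 + 0.38)/2 = 0.54, Z(alpha/2) = 2.394 and Z(beta) = 0.842.

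n = [2.394 × √(2 × 0.54 × 0.46) + 0.842 × √(0.70 × 0.30 + 0.38 × 0.62)]² / 0.32²
= [2.394 × 0.7048 + 0.842 × 0.6675]² / 0.1024 = 49.4, so 50 per arm.

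50/0.95 = 52.6, so 53 per arm, and 3 × 53 = **159**, as stated.

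**Step 2: power of the unadjusted test.** By the same formula it is 80.6% with 50 evaluable per arm and 83.2% with 53. Design and test agree, and the target is met.

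**Step 3: power with adjustment, by formula.** The protocol gives no prognostic strength, so the share R² of variance explained is an assumption. Effective n per arm is 50/(1 − R²).

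| Assumed R² | Effective n per arm | Power |
|---|---|---|
| 0 | 50.0 | 80.6% |
| 2% | 51.0 | 81.5% |
| 5% | 52.6 | 82.9% |
| 10% | 55.6 | 85.2% |
| 15% | 58.8 | 87.5% |
| 20% | 62.5 | 89.7% |

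**Step 4: power by simulation.** Two arms of 50, one normal covariate, 4,000 trials per setting; unadjusted test against a logistic-standardized risk difference. The variance ratio is adjusted over unadjusted.

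| Assumed odds ratio per SD | Unadjusted | Adjusted | Variance ratio |
|---|---|---|---|
| 1 (no value) | 83.6% | 83.2% | 1.01 |
| 1.5 | 82.4% | 83.4% | 0.98 |
| 2 | 82.5% | 85.7% | 0.91 |
| 3 | 82.7% | 89.4% | 0.85 |

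With a likelihood-ratio test in place of the standardized difference, at about 50 to 53 per arm, the change ran from about 1 point lower to 1 point higher for a worthless covariate. It was about 2 to 5 points higher at an odds ratio of 2, and 6 to 9 points higher at 3. One set of runs with two worthless covariates at 50 per arm showed a larger loss (83.2% to 80.7%). At 4,000 trials, the simulation error of one such figure is √(0.83 × 0.17/4000) = 0.6 points.

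**Step 5: type I error.** With both arms at 38% and nominal 0.0167, rejection was 0.016 to 0.019 unadjusted, 0.017 to 0.021 for the standardized difference, and about 0.016 to 0.020 for the likelihood-ratio test. The simulation error is √(0.0167 × 0.9833/4000) = 0.002. The unadjusted test holds its level. The adjusted tests are close to theirs, with slight inflation possible.

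**Step 6: chance imbalance.** For one baseline variable and two arms of 53, P(|difference| > 0.25 SD) = 2 × [1 − Φ(0.25/√(2/53))] = 2 × [1 − Φ(1.287)] = 0.198. This affects the estimate only if the variable is prognostic, and the test's error rate already allows for it.

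**The case against.** The strongest objection is that nothing here is wrong. A crude comparison of randomized arms is valid, the sample size rests on the same comparison, and the planned power is reached. That stands. A reader might infer from the one-in-five chance of a 0.25 SD imbalance that the unadjusted result is biased or its error rate inflated. Step 5 does not support that.

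A reader might also infer that precision is certainly being lost. The protocol does not show this. It nowhere says that age, sex or dizziness history predicts resolution. The 39-day figure is an average for posterior-canal disease generally, not for the cupulolithiasis form studied here. An average time to resolution does not show that elapsed time predicts resolution by the next day; under a constant hazard it would predict nothing.

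Nor is it established that time since onset is already collected. The procedures table lists a dizziness history without its content, and because the inclusion criteria require recurrent attacks, onset may need a definition.

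Finally, covariates are often settled in a statistical analysis plan, which is not at hand. So it cannot be said that adjustment will never be made, only that this protocol does not provide for it. This part of the objection does not remove the point, because the protocol does more than stay silent: it states the outcome method, and that method is unadjusted.

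**Conclusion.** The point holds as a low-cost efficiency improvement. The protocol fixes an unadjusted comparison although baseline values that could be used are collected from everyone at V1, and it gives the demographics only a balance test. It is not a validity defect, and the trial is not underpowered by its own assumptions.

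The size is a range that begins at zero: no gain, or a loss of about 1 point, if the covariates are weak; about 2 to 5 points at an odds ratio of 2 per SD; 6 to 9 points at 3. These figures assume the planning rates of 70% and 38%, about 50 to 53 per arm, alpha 0.0167 and prognostic strengths that the protocol does not supply. The benefit that does not depend on those strengths is that the covariates are chosen before the results are known.

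**What to change.** Replace the outcome sentence in the Study Summary, and add matching text to Section 8, along these lines:

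- The primary analysis of resolution is a logistic regression on arm plus covariates measured at V1 before the maneuver: age, and time since onset of the current episode if the dizziness history records it. If it does not, use age without it. ANOVA, which does not suit a yes/no response, then drops out of the outcome analysis.
- Keep an overall three-arm test followed by all three pairwise comparisons at 0.0167. Say explicitly that this sequence governs the outcome, since the Bonferroni sentence now follows the one on demographics.
- Report covariate-standardized risk differences with confidence intervals. State which result decides, for example the likelihood-ratio test, because a model-based test and a risk-difference interval can occasionally disagree.
- Keep the unadjusted chi-square test as a supportive analysis.
- Present baseline characteristics descriptively, without p-values.

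The cost is a few sentences of text and a few lines of code, with no new visits or participants. The sponsor must check whether the case report form records onset, and must fix the covariates before any outcome by arm is seen. Rare missing baseline values need a rule, such as single imputation. A trivial loss of power is possible if the covariates prove not to be prognostic.

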## ▪ STUDY PROCEDURES

| Study procedure                     | V1              |               | V2 (V1+1day)                                                  |               |
|-------------------------------------|-----------------|---------------|---------------------------------------------------------------|---------------|
|                                     | Treatment group | Control group | Treatment group                                               | Control group |
|                                     |                 |               | When the subjects still have positional vertigo and nystagmus |               |
| Informed consent                    | X               | X             |                                                               |               |
| Demographics assessment             | X               | X             |                                                               |               |
| Inclusion/exclusion criteria        | X               | X             |                                                               |               |
| Medical history                     | X               | X             |                                                               |               |
| Assessment of dizziness history     | X               | X             |                                                               |               |
| Neuro-otological examinations       | X               | X             |                                                               |               |
| Positional test                     | X               | X             | X                                                             | X             |
| Canalith repositioning maneuver     | X               | X             |                                                               |               |
| Determination of treatment response | X               | X             | X                                                             | X             |
| End of study                        |                 |               | X                                                             | X             |

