## **7. METHODS**

### **1) STUDY METHODS**

- A. Subjects with PC-BPPV-cu confirmed and treated at each clinic will be randomly assigned to the treatment groups or to the control (sham) group.

- B. A treatment maneuver was performed by a physician according to the assigned treatments or sham group.
- C. Treatment response was determined by the participating neurologists at each clinic without knowing the maneuver applied to each patient 30 minutes after the initial maneuver.
- D. If the patient had positional vertigo and nystagmus, the previously applied maneuver was repeated.
- E. The patients underwent re-examination 30 minutes later and were scheduled for follow-up the next day without additional treatment if they still presented with positional vertigo and nystagmus.

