### **4) ASSESSMENTS**

- A. The absence of both vertigo and nystagmus was required to determine a resolution.

- B. Evaluation of treatment effect: The efficacy of treatment will be judged by an independent investigator blinded to the subject's information. If there is no improvement after the initial treatment, the patient will receive the same treatment once more. If there is still no improvement, the patient will visit the hospital again the following day for further evaluation.

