### **4) PROCEDURE FOR ACCOUNTING FOR MISSING, UNUSED, AND SUPURIOUS DATA**

Missing values in parameters will be imputed with the Last Observation Carried forward.

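### The primary endpoint is next-day resolution, but the schedule examines only day-1 failures the next day, so overnight relapse cannot be seen and the per-protocol rule misfires

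*Protocol*

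**What the plan says.** Section 7, 5) Trial endpoints, sets the primary endpoint as "The overall short-term resolution rate of positional vertigo and nystagmus in the following day" and the secondary endpoint as "The immediate efficacy of two trials of each maneuver within 30 minutes".

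The next-day visit is described in five places, and each makes it conditional on failure on day 1:

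- Study Procedures table: the V2 columns, which contain the positional test and the response determination, are headed "When the subjects still have positional vertigo and nystagmus".
- The Visit schedule row of the Study Summary reads: "Subjects will be scheduled to return to the clinic the next day if the vertigo and nystagmus will not resolve after two randomized maneuvers".
- Study Summary, Study methods, item 5: the same condition.
- Section 7, 1) Study methods, item E: patients were re-examined after the second maneuver and "scheduled for follow-up the next day without additional treatment if they still presented with positional vertigo and nystagmus".
- Section 7, 4) Assessments, item B: "If there is still no improvement, the patient will visit the hospital again the following day for further evaluation".

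No section arranges a next-day examination or contact for a participant who resolved on day 1.

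On analysis, Section 8, 4) says: "Missing values in parameters will be imputed with the Last Observation Carried forward". Section 8, 1) plans both intention-to-treat and per-protocol analyses of the primary outcome, and leaves out of the per-protocol set anyone without a completed next-day assessment. Section 8, 5) gives a different per-protocol exclusion, tied to use of a web-based system. Neither says how a day-1 responder is scored on the next day.

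**The concern.** The endpoint names a time point at which the schedule does not look at day-1 responders. If their day-1 result stands in for the next day, the outcome can move in one direction only: a day-1 failure may become a success, but a day-1 success can never become a failure. Whether a participant is measured at all depends on day-1 response, which the protocol itself expects to differ between arms.

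Two things are at stake. The first is what the trial may conclude. The stated purpose separates immediate from short-term efficacy, yet for day-1 responders the short-term result adds nothing to the immediate one. The second is whether the per-protocol analysis can be run, since its literal rule removes the very participants who responded.

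**Working it through.** **Inputs.** 53 per arm, 159 in total (Study Summary). Immediate resolution of 70% in each active arm and 38% in sham, alpha 0.0167, power 80%, dropout 5% (Section 8, 2). Relapse and late-resolution rates are not in the protocol; those below are assumptions.

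**Step 1: the plan's own figure.** With the protocol's formula, two-sided and without continuity correction, mean P = (0.70 + 0.38)/2 = 0.54, and

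n = [2.393 × √(2 × 0.54 × 0.46) + 0.842 × √(0.70 × 0.30 + 0.38 × 0.62)]² / 0.32² = 49.4, rounded up to 50.

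50/0.95 = 52.6, so 53 per arm, and 3 × 53 = 159. The stated size reproduces. The sample-size arithmetic is not at fault.

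**Step 2: who has no next-day examination.** Day-1 responders: 0.70 × 53 = 37.1, again 37.1, and 0.38 × 53 = 20.1. The sum is 94.3, or 94.3/159 = 59%. By arm the unexamined share is 70%, 70% and 38%. If the planning rates refer to one maneuver only, which the protocol does not say, the share after two is at least as large.

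**Step 3: the literal per-protocol set.** Only those examined the next day remain: 53 − 37.1 = 15.9, again 15.9, and 53 − 20.1 = 32.9. That is about 16, 16 and 33, all of them day-1 failures.

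**Step 4: what unseen relapse could do.** Let a fraction r_a of active and r_s of sham day-1 responders relapse overnight, and set late resolution to zero. The true next-day difference is

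0.70 × (1 − r_a) − 0.38 × (1 − r_s),

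against a day-1 difference of 0.70 − 0.38 = 32 points.

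| Assumed relapse, active / sham | Next-day rates | Difference |
|---|---|---|
| 0% / 0% | 70.0% v 38.0% | 32.0 points |
| 10% / 10% | 63.0% v 34.2% | 28.8 points |
| 20% / 5% | 56.0% v 36.1% | 19.9 points |
| 5% / 20% | 66.5% v 30.4% | 36.1 points |

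Carrying day-1 results forward overstates the difference when 0.70 × r_a exceeds 0.38 × r_s, and understates it when sham relapse is more than 0.70/0.38 = 1.84 times active relapse.

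**Step 5: late resolution.** The 32 points are the day-1 difference, not the primary result the trial would report. If 10% of day-1 failures in every arm resolved by the next day (assumed), the reported rates would be 0.70 + 0.30 × 0.10 = 73.0% and 0.38 + 0.62 × 0.10 = 44.2%, a difference of 28.8 points before any relapse.

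**Step 6: power at 53 per arm, same test.** With no relapse and no late resolution it is 83%. If everyone were examined and relapse were equal across arms, it would be 78% at 5% relapse, 73% at 10% and 61% at 20%. The size needed for 80% power, before dropout, would be 56, 62 and 77 per arm. Under the cumulative definition, 10% late resolution in every arm gives 74%.

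**The case against.** The strongest reply is that the word *overall* in the endpoint means cumulative resolution: resolved on day 1, or found resolved the next day among the rest. The schedule fits that reading exactly, and the protocol claims only immediate and short-term efficacy. This is a fair reading, and it is one of the two repairs proposed. But the endpoint places resolution in the following day, nothing says how day-1 responders are scored, and relapse stays unobserved either way. A separate analysis plan could settle the scoring, but it cannot supply an examination that the protocol does not schedule.

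A reader might go further and infer three things that the protocol does not support:

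- *That the bias favours the active arms.* They would hold more unverified successes, and under equal relapse the risk difference would be overstated. But the protocol gives no relapse rates, and the direction reverses once sham relapse exceeds about 1.84 times active relapse. Under equal relapse the risk ratio does not change (0.63/0.342 = 0.70/0.38 = 1.84).
- *That the protocol prescribes carry-forward for responders.* The rule covers missing values. Whether an unscheduled examination counts as missing is not stated, and the per-protocol rule points the other way.
- *That most outcomes are unobserved in every arm.* This holds overall and in both active arms, but not in sham (38%).

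**Conclusion.** The point holds as a mismatch between the primary endpoint and its ascertainment. At the protocol's own planning rates, about 94 of 159 participants (59%; 70%, 70% and 38% by arm) would have no observed next-day status. Overnight relapse cannot be seen, and the per-protocol rule in Section 8, 1), taken literally, leaves an analysis of day-1 failures only.

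The counts rest on the planning rates. The scoring of responders is inferred from the schedule together with the missing-data rule. The range of 19.9 to 36.1 points around a day-1 difference of 32 rests on assumed relapse rates and no late resolution. It shows that neither the size nor the direction of a bias can be known from this design; it does not show that the active arms are favoured.

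**What to change.** Make the primary endpoint match what is observed, in one of two ways:

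1. Make resolution 30 minutes after the last maneuver the primary endpoint. It is observed on day 1 in everyone, and the planning rates are labelled as immediate resolution, so the 159 stays supported. The next-day measure becomes secondary.
2. Keep the present primary endpoint but define it as cumulative resolution by the next day, with day-1 responders not re-examined and counted as resolved. The planning rates should then be restated to allow for late resolution (Step 6).

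In either case, amend Section 8, 1) so that day-1 responders stay in the per-protocol set, reconcile it with Section 8, 5), and make no claim of sustained next-day resolution. The cost is an amended endpoint section and a narrower claim; no new visit is needed.

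The alternative is a blinded V2 positional test, as an outcome assessment, in all randomised participants. That measures the endpoint as stated. It needs about 94 more visits at the planning rates, and the power would have to be restated (about 73% at 53 per arm under 10% relapse in every arm). It must be decided before those participants pass day 2, because the missing observation cannot be recovered later.
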